### Effectiveness outcomes

Primary effectiveness outcomes are:*Family health-related quality of life*: measured using the caregiver self-reported Pediatric Quality of Life Family Impact module (PedsQL) [31]. The PedsQL assesses the impact of pediatric chronic health conditions (here developmental disability and associated at risk conditions) on caregiver physical, social, emotional, cognitive, wellbeing, communication and worry, as well as the impact on family activity and family relationships. Scores are categorised into total, caregiver health-related quality of life and family functioning. *Child participation*: measured using the Young Children’s Participation and Environment Measure (YC-PEM) [32]. The YC-PEM is a caregiver-completed measure that investigates the participation of children aged 0–5 in activities across home and the community. Scores are categorised into frequency, involvement and desire for change. The tool will be adapted and validated for use in this Rwandan population and setting.

Secondary effectiveness outcomes are:*Caregiver knowledge and confidence*: measured using an adapted version of the World Health Organization pre- and post-Parent Skills Training Test for Caregivers [33].*Caregiver psychological distress*: assessed via the Self-Reporting Questionnaire (SRQ) [34].*Caregiver experience of disability-related stigma*: measured using the Affiliate Stigma Scale [35].*Caregiver economic activity*: measured using a time-use survey from the Living Standards Measurement Survey [36].*Child mortality*: confirmed by caregiver report, community health worker or electronic medical records. Recorded at endline only.*Childhood hospital admission due to illness*: hospitalisations (defined as admission of one or more nights) in the past 12 months on caregiver report. Recorded at endline only.*Child development and function*: measured via the development-for-age Z-scores (DAZ) on the Global Scales of Early Development (age 0–3 years) [37], the Malawi Development Assessment Tool (age > 3 years) [30], and the Pediatric Evaluation of Disability Inventory - Computer Adaptive Test (PEDI-CAT) [38].*Child growth and nutritional status*: defined as weight-for-age (underweight), height-for-age (stunting), based on World Health Organization Growth Standards [39].

In addition, we will assess several exploratory outcomes. Experiences of early intervention will be assessed using the Family Outcomes Survey [40], child supervision and child discipline will be assessed using questions from UNICEF’s Multiple Indicator Cluster Survey (MICS) Questionnaire for children under five [41].The need for, and access to, disability-related goods and services, such as healthcare and assistive technology, will be recorded through caregiver report.

### Implementation outcomes

Primary implementation outcomes are feasibility and acceptability. Feasibility for families will be assessed by the proportion of those eligible to access the intervention who go on to utilise intervention services (attendance). Acceptability for families will be measured as the proportion with satisfactory programme adherence (≥ 60% sessions). Acceptability for community health centres will be defined as the proportion of approached health centres that go on to implement the programme. Secondary implementation outcomes will be fidelity, cost and cost-effectiveness (detailed under *Process and economic evaluation*).

### Data collection

Screening, informed consent and baseline/endline survey data collection will take place at health centres. Trained data collectors will collect survey data via structured interview with the child’s primary caregiver. Developmental progress will be assessed on direct assessment of the child using standardised, culturally-relevant developmental assessment tools. Data collectors will receive training for one week, including pilot for assessment and feedback. Pilot data will be used in the final analysis, dependent on data quality. All data collection tools will be translated into Kinyarwanda and back translated into English before finalisation. Data collection general procedures will be guided by a Standard Operating Protocol. Participants will be provided remuneration for participating in the baseline/endline survey and for transport (total 6,000 RWF).

### Blinding

The Principal Investigators and outcome assessment team will be blinded to the allocation status of trial participants. The outcome assessment team will be independent to the intervention delivery team and will be blinded to allocation at all outcome assessment timepoints. Given the nature of the intervention, it is not possible to blind participants. We do not anticipate any requirement for unblinding, but if required, the Principal Investigators will have access to group allocations and unblinding will be reported.

### Sample size

The primary analysis will be conducted amongst all children at risk of developmental disabilities and their caregivers. Secondary analysis will be conducted for the sub-population of children with developmental disabilities. Sample size calculations are based on the primary effectiveness outcomes amongst the sub-population of children with developmental disabilities, as this is the population for which data were available and is an important secondary analysis population. As a result, the trial will be powered to detect smaller intervention effects for the primary analysis population of all at risk children. We assume 10 clusters per trial arm with 35 children with developmental disabilities per cluster, for a total of 700 children with development disabilities overall, of whom 20% will not consent to participate in the evaluation or will be lost to follow-up. This results in a total of 560 children with developmental disabilities with outcome data (280 in each trial arm, 28 per cluster). Previously published data from a Ugandan cohort of children (< 3 years) with developmental disabilities suggest a mean family health-related quality of life score (PedsQL) of 60 amongst care as usual families (standard deviation 20) [28]. Data from Brazil suggest a mean YC-PEM home participation frequency raw score of 59 (standard deviation 7.5) and a mean YC-PEM home participation involvement raw score of 43 (standard deviation 7.5) in those receiving standard care [42]. Based on these values, Table 2 indicates detectable differences for family health-related quality of life and child participation among children with developmental disabilities, with 80% power and 5% significance level, for a range of intra-cluster correlation coefficient (ICC) scenarios. Detectable differences are shown as absolute difference, relative difference and as Cohen’s effect size.

**Table 2 Tab2:** Detectable differences in family health-related quality of life and child participation primary outcomes

	**Intra-cluster correlation coefficient**		
Outcome	0.01	0.05	0.1
PedsQL^1^	Absolute difference: 5.6 Relative difference: 9.4%Cohen’s effect size: 0.28	Absolute difference: 7.7Relative difference: 12.8%Cohen’s effect size: 0.39	Absolute difference: 9.6Relative difference: 16.0%Cohen’s effect size: 0.49
YC-PEM frequency^2^	Absolute difference: 2.1Relative difference: 3.6%Cohen’s effect size: 0.28	Absolute difference: 2.9 Relative difference: 4.9%Cohen’s effect size: 0.38	Absolute difference: 3.6 Relative difference: 6.1%Cohen’s effect size: 0.48
YC-PEM involvement^3^	Absolute difference: 2.1Relative difference: 4.9%Cohen’s effect size: 0.28	Absolute difference: 2.9 Relative difference: 6.7%Cohen’s effect size: 0.38	Absolute difference: 3.6 Relative difference: 8.4%Cohen’s effect size: 0.48

^1^Assuming SD 20 and mean PedsQL score of 60 among control arm participants; ^2^Assuming SD 7.5 and mean YC-PEM frequency raw score of 59 among control arm participants; ^3^Assuming SD 7.5 and mean YC-PEM involvement score of 43 among control arm participants

Based on data from the pilot feasibility parallel arm randomised-controlled trial of Baby Ubuntu in Uganda [28], an intra-cluster correlation coefficient of 0.1 is a conservative assumption. We will therefore have 80% power to detect an absolute difference in mean PedsQL between trial arms of 9.6, and an absolute difference in mean YC-PEM frequency and involvement scores between trial arms of 3.6 and 3.6, respectively, equivalent to a Cohen’s effect size of 0.48–0.49. If the intra-cluster correlation coefficient is smaller, at 0.05, we will have 80% power to detect differences between trial arms of 7.7, 2.9, and 2.9 for these outcomes, respectively. These differences are smaller than those observed for the PedsQL in Uganda and the YC-PEM in Brazil [28, 42]. We estimate that half of children at risk of developmental disabilities will have a disability and will thus aim to recruit around 1,400 at risk children, inclusive of 700 at high risk of developmental disabilities.

### Data management

Trial data will be collected and stored in compliance with Rwanda Law No 058/2021 relating to the protection of personal data and privacy, the General Data Protection Regulation (GDPR) 2016/679 of the European Parliament and the Council of the European Union, and the London School of Hygiene & Tropical Medicine Research Data Management Policy. A Data Protection Impact Assessment will be developed and approved by the London School of Hygiene & Tropical Medicine Data Protection Officer to minimise data protection risks.

Hard copies of data (e.g. signed consent forms, qualitative interview notes) will be stored in locked, secure cabinets. Baseline and endline survey data will be collected electronically using REDCap on password protected tablets and uploaded to a secure, password-protected server in Rwanda. A master file linking participants’ names with ID numbers, signed consent forms, and contact information will be stored in an encrypted file separate from the data files.

Anonymised data will be shared with the London School of Hygiene & Tropical Medicine using a secure data-transfer protocol and stored on a secure, password-protected server. Twelve months after the end of the project, data will be made available on the London School of Hygiene & Tropical Medicine Data Compass (datacompass.lshtm.ac.uk), an open access public data repository, along with project documentation and a data-user guide. Data available on the repository will include no identifiers. Data will be made available upon request, provided the requester has a legitimate purpose for using the data. Participants will provide explicit consent for anonymised data to be made available on the Data Compass. Availability of data will be contingent on relevant approvals under Rwanda Law No 058/2021 relating to the protection of personal data and privacy.

### Data analysis

The trial will adopt a superiority design, evaluating whether the PDC/Baby Ubuntu intervention is superior to enhanced usual care in improving primary and secondary outcomes. Analyses will follow intention-to-treat principles. Clusters will be analysed according to their original randomisation, regardless of coverage or other variables.

The full analysis set will consist of all randomised subjects analysed according to the study arm to which they were assigned. The primary analysis will focus on all children at risk of developmental disabilities and their caregivers, comparing those receiving the PDC/Baby Ubuntu programme to the control group. The secondary analysis will compare children with developmental disabilities and their caregivers who received Baby Ubuntu to children with developmental disabilities in the control group. Superiority will be demonstrated if there are statistically significant improvements in the intervention arm versus the control arm for the prespecified outcomes.

Because of the relatively small number of clusters (n ≤ 20), cluster-level analyses will be used to assess the overall effect of the intervention. Specifically, in crude analyses, cluster-level means for each outcome measure will be generated and compared using t-tests. Adjustment for district and cluster size will be done using the two-stage approach described by Hayes and Moulton [43].

In further prespecified exploratory analyses, we will also analyse data at the individual level using generalised linear models (with an appropriate link function depending on the type of data) with random effects to allow for clustering of individuals. As this is not a confirmatory study, we do not plan any formal adjustment for multiple testing. Missing data will be handled using complete case analysis as the primary approach. Multiple imputation methods may also be used as a sensitivity analysis if substantial missing data exists (> 10% missing).

Subgroup analyses will assess whether the effect of the intervention may differ by variable, considering but not limited to socio-demographic status (e.g. maternal age, education, poverty), social support e.g. paternal abandonment/family structure/living situation; severity of disability; age of child at entry into the programme; locality (urban/rural). Any additional post-hoc analyses will be explicitly described as such in the final publication. Additional exploratory analyses will also consider non-randomised comparisons, such as investigation of dose response relationships within the intervention group.

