**Methods:**

The study is a single-blind, effectiveness implementation-hybrid (type II) cluster randomised controlled trial with two arms (1:1 ratio). At cluster level, all community health centres in the three trial districts will be eligible for inclusion. At the participant level, at risk children aged ≤ 59 months will be eligible where ‘at risk’ is defined as being a survivor of a newborn condition that is a recognised risk factor for developmental disability (neonatal encephalopathy, prematurity, meningitis, severe jaundice, cerebral malaria, suspected genetic and chromosomal conditions and seizures), and/or not meeting age-specific developmental milestones. Those receiving inpatient hospital treatment or in institutional care will not be eligible. Primary outcomes will be family health-related quality of life (PedsQL) and child participation (Young Child Participation & Environment Measure) assessed 12 months after enrolment and randomisation. Secondary outcomes include caregiver knowledge and confidence (scored structured assessments), psychological distress (Self-Report Questionnaire), experience of disability-affiliated stigma (Affiliate Stigma Scale), and economic activity (time-use survey), in addition to child mortality, illness and hospitalisation, child development/function (Global Scales of Early Development, Malawi Developmental Assessment Tool, PEDI-CAT), and nutritional status (weight-for-age, height-for-age). Analysis will be by intention-to-treat, consisting of all randomised subjects analysed according to assigned study arm. Cluster-level analyses will assess intervention effect.

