### Intervention description

The Pediatric Development Clinic (PDC) is an interdisciplinary model established in 2014 by Partners in Health/Inshuti mu Buzima (PIH/IMB) and the Rwanda Biomedical Centre (Ministry of Health) to monitor and provide targeted support within the public health system for children at risk of developmental delay and disability due to perinatal risk factors [23, 24]. Providers are non-specialised healthcare professionals, primarily general nurses and social workers. They are trained and mentored to deliver a structured package of neonatal follow-up and early intervention services based on components of nurturing care. Children enrolled in PDC are systematically followed up and are discharged from the programme at 36 months if they are developmentally on-track without any health or nutritional problems. PDCs implemented in Rwanda have demonstrated feasibility and improved child and caregiver outcomes [23, 24]. In a quasi-experimental study, post-neonatal unit mortality declined from 12 to 9% (p < 0.05), with a larger decline amongst preterm and low birth weight infants, reducing from 12.4% to 5.9% (p < 0.001).

Children attending the PDC who have severe developmental delay, assessed via the Guide for Monitoring Child Development (GMCD) [25], are referred to the Baby Ubuntu programme. Baby Ubuntu is a participatory, group-based, peer-led rehabilitation programme providing early care and support for young children with developmental disabilities and their caregivers. Group sessions are co-facilitated by community or facility-based healthcare professionals and ‘Expert Parents’, themselves parents of children with developmental disabilities. The content is divided into 11 modules, including information on understanding disability, positioning and carrying, feeding, communication, play, and experiences in the local community. Each session lasts for 2–3 hours. Evidence from mixed-methods, pre-post intervention evaluations of Baby Ubuntu in both urban and rural settings in Uganda have indicated a 20–25% increase in family and child health-related quality of life [26, 27]. A pilot feasibility, randomised-controlled trial in Uganda showed the programme to be both feasible and acceptable to families and health care workers in both rural and urban settings [28].

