**Fig. 2 Fig2:**
[figure not shown]
The Pediatric Development Clinic/Baby Ubuntu bundle

For this trial, the combined PDC/Baby Ubuntu bundle will be delivered in intervention cluster health centres as part of routine government child health services. Recruited children in the intervention clusters will be invited to the PDC at the health centre at which they completed the baseline survey. Children identified as having a developmental disability will be invited to join the Baby Ubuntu programme.

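### The secondary disability analysis conditions on receipt of Baby Ubuntu in the intervention arm only, contradicting the intention-to-treat statement and the sub-population used for sample size

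*Protocol article*

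**What the plan says.** The Data analysis section opens with a general commitment: "Analyses will follow intention-to-treat principles". It adds: "Clusters will be analysed according to their original randomisation, regardless of coverage or other variables". Its analysis set is equally plain: "The full analysis set will consist of all randomised subjects analysed according to the study arm to which they were assigned". The abstract repeats the commitment.

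The same section then gives the secondary analysis as a comparison of "children with developmental disabilities and their caregivers who received Baby Ubuntu to children with developmental disabilities in the control group".

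The Sample size section describes that analysis differently: "Secondary analysis will be conducted for the sub-population of children with developmental disabilities". It has no condition on receipt. It calls this an important secondary population and bases the sample size on it, with 28 children per cluster in each arm.

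The Intervention description gives the route into Baby Ubuntu. For the PDC model in general, those referred on are "Children attending the PDC who have severe developmental delay, assessed via the Guide for Monitoring Child Development (GMCD". For this trial it says: "Children identified as having a developmental disability will be invited to join the Baby Ubuntu programme".

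The Baseline data section says disability status at baseline will be determined with the Malawi Developmental Assessment Tool (MDAT). It then defines moderate to severe disability as a development-for-age Z-score (DAZ) below −2 at endline, because classification is more reliable in older children.

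**The concern.** Clusters are randomised after the baseline assessment. To count as having received Baby Ubuntu, a family in an intervention cluster must then attend the PDC, be identified there and take up an invitation. None of these steps exists in control clusters. If the sentence is followed literally, disabled children whose families never attended, were not referred or declined drop out of the intervention side, while their counterparts stay in the control side.

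The groups then differ by whatever separates recipients from non-recipients. More engaged or better-supported families may be over-represented, which would favour the programme. Families of more severely affected children may be over-represented, which would count against it. Either way a difference can appear when the programme does nothing.

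Incomplete uptake is a real possibility in this plan, since the Implementation outcomes section makes attendance among eligible families a primary implementation outcome. The last paragraph of Data analysis places non-randomised comparisons under additional exploratory analyses, but does not list this contrast there. The section's superiority criterion, which rests on statistical significance, is stated straight after the secondary analysis and does not exclude it.

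**Working it through.** **1. The plan's own figure.** Inputs from the Sample size section and Table 2: c = 10 clusters per arm, m = 28 disabled children per cluster with outcome data (700 × 0.8 = 560, or 280 per arm), PedsQL SD 20, ICC 0.1, 80% power, 5% significance (two-sided assumed).

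Design effect = 1 + (28 − 1) × 0.1 = 3.7.

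Detectable difference = (1.960 + 0.842) × √[2 × 20² × 3.7 / (28 × (10 − 1))] = 2.802 × √(2960/252) = 2.802 × 3.427 = 9.60. The plan states 9.6. The other eight absolute differences in Table 2 also reproduce.

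The calculation uses 28 per cluster in both arms, that is, all disabled children with outcome data. It therefore matches the population in the Sample size section and not the as-received contrast in Data analysis.

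**2. Standard error by allocation.** 20 × √(2 × 3.7 / 280) = 3.25 points.

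**3. Bias from conditioning on receipt.** Let a proportion u of disabled children in the intervention arm receive Baby Ubuntu, and let recipients and non-recipients differ by g SDs of PedsQL for reasons other than the programme. The mean of all is u × (recipient mean) + (1 − u) × (non-recipient mean), so

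recipient mean − mean of all = (1 − u) × g × 20.

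With no true effect, randomisation makes the mean of all equal to the control mean in expectation, so this quantity is the bias. Its sign follows the sign of g. Rejection rates come from a two-sided t-test on cluster means (18 df) with 28u recipients per intervention cluster and ICC 0.1.

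| Assumed uptake u | Bias, g = 0.2 | Bias, g = 0.5 | Rejection, g = 0.2 | Rejection, g = 0.5 |
|---|---|---|---|---|
| 95% | 0.05 × 0.2 × 20 = 0.2 | 0.05 × 0.5 × 20 = 0.5 | 5.0% | 5.2% |
| 80% | 0.20 × 0.2 × 20 = 0.8 | 0.20 × 0.5 × 20 = 2.0 | 5.6% | 8.9% |
| 60% | 0.40 × 0.2 × 20 = 1.6 | 0.40 × 0.5 × 20 = 4.0 | 7.3% | 20.2% |

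At smaller ICCs the standard error falls and the same bias matters more: at 60% uptake and g = 0.5, rejection is 27.9% at ICC 0.05 and 42.5% at ICC 0.01. Uptake and g are assumptions; the document gives neither for this trial.

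**4. Precision.** Counting only recipients also shrinks the intervention side. At ICC 0.1 the detectable difference would be 9.63, 9.75 and 9.98 at 95%, 80% and 60% uptake. This is minor beside the selection problem.

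**The case against.** The best defence is that the word is loose and means allocated. The sentence on the primary analysis also speaks of those receiving the programme, yet it covers all at-risk children and follows directly after an analysis set defined by assigned arm. The sentence after the secondary analysis again contrasts the two arms. This is plausible, and it is why the point is a contradiction to resolve rather than proof that an as-received design was intended. It does not settle the matter. In the primary sentence the phrase names the whole allocated bundle; in the secondary sentence it names one component, which only referred and invited families reach.

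A second defence is high uptake. The Intervention description reports satisfactory attendance in 95% of pilot families, and at 95% the bias is negligible. But those families were already enrolled in groups, so the figure says nothing about children who never attended the PDC, were not referred or whose families declined.

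A third is that the analysis is secondary, that the primary analysis is untouched and that the article calls the study not confirmatory. All of that stands and limits the reach of the point.

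A reader might also infer that the two sides are classified by different instruments: the Guide for Monitoring Child Development (GMCD) in intervention clusters and something else in control clusters. The document does not support this. Data analysis uses the same label on both sides, and Baseline data gives an MDAT definition that names no arm. The GMCD is a referral step. It acts as an extra one-sided filter only through the receipt condition. Nor can a bias from severity-based referral be sized from the document, which gives neither a DAZ cut-off for referral nor a DAZ distribution.

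**Conclusion.** The point holds as an internal contradiction in a secondary analysis. Data analysis restricts the intervention side by a post-randomisation event, while its own intention-to-treat statements and the Sample size section do not. If the sentence is carried out as written, the result is an observational contrast presented alongside randomised ones.

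The size is uncertain. For a gap of 0.2 to 0.5 SD the bias runs from 0.2 points (95% uptake) to 4.0 points (60% uptake), that is, from negligible to slightly more than one standard error of 3.25. The direction is not known.

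Two stronger readings should be resisted. The sample size is not wrong on this account: Table 2 was computed for the allocation-based population. The primary analysis of all at-risk children is not compromised either.

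**What to change.** Replace the sentence on the secondary analysis with wording such as: *The secondary analysis will include every child classified as having a developmental disability under one common rule, applied identically in both arms, and will compare arms by cluster allocation whether or not the family attended the PDC or Baby Ubuntu.* Move any contrast restricted to Baby Ubuntu recipients to the exploratory non-randomised comparisons at the end of Data analysis, labelled as such.

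Reconcile the timing of the rule with Baseline data. Endline status was chosen there for reliability, but it is measured after randomisation and the programme could affect it, so even an allocation-based subgroup defined at endline can be selected differently by arm. Use baseline MDAT status for the main contrast, or at least as a sensitivity analysis. The drawback is less reliable classification at younger ages, and the analysed population changes somewhat.

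Reconcile the two statements in the Intervention description on who is referred to Baby Ubuntu (severe delay in one, developmental disability in the other).

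Cost: a change of wording in the protocol and analysis plan, with no new data provided the baseline MDAT was recorded as described. The detectable difference stays at 9.6. Non-attenders will dilute the effect: if recipients gained 9.6 points and non-recipients nothing, the allocation-based effect would be 0.8 × 9.6 = 7.7 points at 80% uptake (power about 61% at ICC 0.1) and 0.6 × 9.6 = 5.8 at 60% (about 39%). That diluted effect is the one relevant to offering the programme. Trial status says no data had been analysed at submission, so the change should be made and dated before analysis starts.

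### Read literally, the secondary analysis in children with disabilities filters only the intervention arm on receipt of Baby Ubuntu, against the protocol's own by-assigned-arm rule

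*Protocol article*

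**What the plan says.** The Data analysis section sets the general rule twice: "Clusters will be analysed according to their original randomisation, regardless of coverage or other variables", and "The full analysis set will consist of all randomised subjects analysed according to the study arm to which they were assigned". The Abstract (Methods) agrees: "Analysis will be by intention-to-treat, consisting of all randomised subjects analysed according to assigned study arm".

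The same section then describes two comparisons. The primary one covers all at-risk children, "comparing those receiving the PDC/Baby Ubuntu programme to the control group". The secondary one compares "children with developmental disabilities and their caregivers who received Baby Ubuntu to children with developmental disabilities in the control group".

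The Sample size section describes the secondary population differently: "Secondary analysis will be conducted for the sub-population of children with developmental disabilities". It plans on "560 children with developmental disabilities with outcome data (280 in each trial arm, 28 per cluster"), and these figures underlie Table 2. No receipt condition appears there.

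On the route into Baby Ubuntu, the Intervention description says: "Children identified as having a developmental disability will be invited to join the Baby Ubuntu programme". It also says that children attending the PDC with severe delay on the GMCD are referred. Under Implementation outcomes, the share of eligible families who use the services is an outcome to be measured. Non-randomised comparisons are listed at the end of Data analysis as exploratory, and the secondary comparison is not among them.

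**The concern.** The two sides of the secondary comparison are defined by different rules. A control child enters by having a disability. An intervention child enters by having a disability and having received Baby Ubuntu, which requires reaching the PDC, being identified there and joining a group. None of these steps occurs in a control cluster, so no matching filter can be applied to that arm.

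Families who complete the route may differ from those who do not, for example in motivation, distance from the health centre or the child's severity. Randomisation does not balance a subset chosen this way, and the direction of the resulting bias is unknown. The Sample size section calls this population important and bases the trial's size on it, so which children enter it matters. Two analysts could also build different datasets from the present text.

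**Working it through.** **1. Reproduce Table 2.** Inputs from the Sample size section: SD 20 for PedsQL and 7.5 for both YC-PEM scores, 10 clusters per arm, 28 children per cluster, 80% power, 5% significance (taken as two-sided), ICC 0.01, 0.05 and 0.1. For a t-test on cluster means with 18 df (critical value 2.101), let the intervention arm have 28r children per cluster:

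SE = √{ (SD²/10) × [ (ICC + (1 − ICC)/28) + (ICC + (1 − ICC)/(28r)) ] }

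With r = 1 and the non-central t, the detectable PedsQL differences are 5.64, 7.68 and 9.63 (Table 2: 5.6, 7.7, 9.6). For YC-PEM they are 2.12, 2.88 and 3.61 (Table 2: 2.1, 2.9, 3.6). Table 2 is reproduced with 280 children per arm.

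**2. Precision if the arm is filtered.** At ICC 0.1 the detectable PedsQL difference moves from 9.6 to 9.7 at r = 0.95 and 9.8 at r = 0.75. The loss is small. Selection is the issue, not power.

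**3. Bias under no effect.** Let receivers have mean R and non-receivers mean N in the absence of the programme, with d = R − N. By randomisation the control arm has the same mixture, with mean rR + (1 − r)N. Then

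bias = R − [rR + (1 − r)N] = (1 − r) × d.

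The documents give neither r nor d. I assume d = 5 to 10 PedsQL points (0.25 to 0.5 SD) and show two values of r. The 0.95 is borrowed from satisfactory attendance in the Rwandan pilot (Intervention description); 0.75 is illustrative.

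**4. Rejection rate of the nominal 5% test with no true effect** (non-central t, non-centrality (1 − r)d/SE):

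| r | d | Bias | ICC 0.05 | ICC 0.1 |
|---|---|---|---|---|
| 0.95 | 5 | 0.25 | 5.09% | 5.06% |
| 0.95 | 10 | 0.50 | 5.38% | 5.24% |
| 0.75 | 5 | 1.25 | 7.27% | 6.47% |
| 0.75 | 10 | 2.50 | 14.34% | 11.02% |

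The SEs used are 2.605 and 3.262 at r = 0.95, and 2.677 and 3.317 at r = 0.75.

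**5. Direction.** The protocol counts only improvements as superiority, nominally 2.5%. At r = 0.75 the false-superiority rate is 5.45–14.12% if receivers would have done better anyway, and 0.22–1.02% if they would have done worse.

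**6. Where it starts to matter.** Two-sided rejection reaches 10% when r falls to 0.82 (ICC 0.05) or 0.77 (ICC 0.1) with d = 10, and to 0.62 or 0.53 with d = 5.

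**The case against.** The strongest reply is that the phrase is shorthand. The Methods introduction says intervention clusters will receive the programme, and Randomisation describes each arm as receiving its care, so the protocol does use the verb for allocation. The disputed sentence follows the by-assigned-arm statement, and the next one judges superiority between arms. Since Baby Ubuntu is the component offered to children with a disability, naming it for that subgroup is natural. This reading is plausible, and it is why the primary sentence can be taken as assignment to the arm. It is less secure for the secondary sentence, which names one component that a child reaches only after several steps, and whose uptake the protocol treats as unknown. The ambiguity remains.

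The size of the problem is also conditional. Both r and d are assumptions, and at r = 0.95 nothing of note happens. However, the pilot's 95% concerns families already enrolled in Baby Ubuntu groups. It does not estimate the share of all intervention-arm children with a disability who reach a group, so it can neither reassure nor alarm.

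A reader might infer that Table 2 proves the receipt condition was never intended. It does not. At r = 0.95, seven or eight of its nine absolute differences still round to the printed values, depending on the formula. The evidence is the stated 280 per arm, not the detectable differences.

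Finally, this is a secondary analysis in a trial that describes itself as not confirmatory, and a separate analysis plan may define the set. That limits the reach, but the article does state a population, and it conflicts with its own rule.

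**Conclusion.** The point holds as an inconsistency with conditional consequences. Read literally, the secondary comparison conditions one arm on a post-randomisation event, contrary to the intention-to-treat statements and to the Sample size section. The documents do not show that it will be run that way, so it would be wrong to say that the trial plans a per-protocol secondary analysis, or that the stated error rate is already lost.

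If it is run literally, the bias is (1 − r) × d, in an unknown direction. With an assumed d of 5 to 10 PedsQL points and ICC 0.05 to 0.1, rejection under no effect is 5.1–5.4% at r = 0.95 and 6.5–14.3% at an illustrative r = 0.75. The primary analysis, if run by arm, is not affected, and Table 2 stands. The correction should be made because this population sized the trial and the change is cheap. Confidence is medium, given the plausible shorthand reading.

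**What to change.** In Data analysis:

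- In the secondary sentence, replace *who received Baby Ubuntu* with *in the intervention arm*, and state that one disability definition applies identically in both arms, whether or not a child was invited to or attended Baby Ubuntu.
- Preferably take that definition from the baseline MDAT, which is collected before randomisation. The Baseline data section instead sets DAZ < −2 at endline, on the ground that diagnosis is more reliable in older children. That is a fair reason, but the measure comes after randomisation and child development is a secondary outcome, so the programme could change who enters the set. If the endline definition is kept, say so and add the baseline definition as a sensitivity analysis.
- In the primary sentence, change *those receiving* to *those assigned to*.
- Move any receiver-only comparison to the exploratory non-randomised analyses.

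The cost is wording only; no new data are needed. Trial status reports that endline assessment was incomplete and no data had been analysed at submission, so the change could then still be prespecified.

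The statistical price is dilution. In the worst case, where children who miss Baby Ubuntu gain nothing (they may still attend the PDC), the by-arm effect is r times the effect in receivers. At ICC 0.1, an effect in receivers of 9.63 becomes 0.95 × 9.63 = 9.15 or 0.75 × 9.63 = 7.22, and power falls from 80% to 76% or 56%. The same powers apply at ICC 0.05 with 7.68. This is the ordinary price of the intention-to-treat rule the protocol has already adopted.
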